#### Questionnaires

In addition to a simple baseline demographics questionnaire, we will ask all parents about their child’s involvement in extra-curricular activities (sport, dance, music, art playgroups), and potential behaviour change at home (which will be validated by accelerometer data) so that we can account for participation in the analyses. We will collect information about the child’s health-related quality of life using the PedsQL^TM^ Measurement Model for the Pediatric Quality of Life Inventory instrument. The PedsQL^TM^ Measurement Model is a modular approach to measuring health-related quality of life from a multidimensional standpoint (physical, social, emotional, and school functioning) in children and adolescents. The tool is practical as it takes 4 minutes to complete and is reliable (internal consistency for the Total Scale Score: alpha = 0.88 Child Self-Report; alpha = 0.90 Parent Proxy-Report) [65].

The physical childcare environment will be rated using the relevant items from the validated Environment and Policy Assessment and Observation (EPAO) instrument. Construct and predictive validity of the physical activity environment domains, as well as inter-observer reliability of the EPAO instrument have been published previously [66–69]. The PA child behaviours portion of the EPAO instrument, created to evaluate a US-based healthy active living childcare program, is easily applied in the Canadian setting as it assesses the accessibility of the physical environment and facilities within the daycare setting that may promote or restrict PA.

Intervention daycare providers and parents will complete a questionnaire prior to the workshop/webinar training that assesses attitudes, control beliefs, perceived competence, and intentions, as well as support for increasing PA based on the Theory of Planned Behaviour [70, 71]. Following the workshop they will complete another that focuses on their understanding of the central health messages associated with ABC program.

#### Cost analysis

A cost analysis will also be conducted to evaluate the costs of delivering the ABC intervention with the outcomes achieved to provide a valuable analytical framework to guide decision making by those who are responsible for allocating resources.

### Process evaluation

Investigators will measure intervention implementation, defined by Fixsen et al. [72] as the “*specific set of activities designed to put into practice an activity or program of known dimensions*”. Experts in implementation measurement [73–75] have identified a set of key measures and for ABC Trial purposes we will focus on: i) fidelity – comparing actual program component delivery to planned delivery (i.e., workshops**/**webinars delivered/attended**/**accessed online by parents*,* booster sessions delivered as scheduled, postcards delivered to parents as scheduled, site observations, environmental assessment, use of resources and materials); ii) dose delivered by daycare providers (i.e., daily activity checklist, site observations, provider engagement during booster sessions, environmental assessment) or dose received by children (i.e., site observations, environmental assessment, PA assessment on preschoolers); iii) the quality of program delivery (i.e., site observation, environmental assessment, booster session feedback); iv) responsiveness of program participants (i.e., observations); and v) adaptations made to program during implementation (i.e., responsive to daycare provider feedback by incorporating online and hard copy materials, providing additional contact with providers, more example-based workshop material, incorporate FUNdamentals framework). Additionally, we will assess perceived competence, control beliefs, and intentions of both daycare providers and the parents who are involved in the Home Component. The process evaluation methods will include both direct (i.e., EPAO, Actical^®^) and indirect methods (i.e., daily activity checklist). Data from all of these sources will be pooled to assess fidelity and completeness of the implementation in both the daycare and home environment (for participants who receive the Home Component). Further, on a bi-monthly basis, the Master Trainer and Research Coordinator conduct semi-structured interviews with daycare providers to assess any potential barriers/obstacles to implementation of the ABC programming.

### Sample size

The proposed study design is a cluster-randomized trial, where individual preschoolers are nested in daycare centres (clusters). Because observations within clusters are expected to be correlated, the total number of preschoolers that need to be enrolled is larger than would be the case if it were feasible to randomize them individually. This is known as the design effect for a cluster-randomized trial, and it depends on the cluster size(s) and the intra-cluster correlation (ICC). The sample size, therefore, should be multiplied by the design effect (D) [76] (i.e., D = 1 + (m–1) × ICC, where m is cluster size and ICC is the intra-cluster correlation coefficient of the outcome measure).

Licensed daycare centres in the NCR typically enroll between 10 and 40 preschool children, depending on the size of the centre and number of staff. To be conservative, the assumption is that there is an average of 15 preschoolers from each daycare. The estimate of ICC used for the present study was obtained from a similar cluster-RCT, exploring the effectiveness of an elementary school-based PA program aimed at impacting body fat, fitness, and PA, which reported an ICC for MVPA of 0.08. [77] The sample size calculation was performed using the sample size calculator for cluster randomized trials of Campbell et al. [78]. For the primary comparison between the daycare group and the control group, a total of 12 daycare centres (6 per group) is required to achieve a power of 80% to detect a difference between groups in MVPA of 15 min/day with the probability of type-I error fixed at 5%. Since a third group, DC + HOME, will also be studied, an additional 6 daycare centres will be enrolled, for a grand total of 18 daycare centres. The difference of 15 minutes/day was selected for two reasons; i) we felt it clinically relevant given the recent systematic review by Janssen et al. [79] indicating that health benefits may be achieved with an average of 30 min of MVPA/day (at least in elementary school children) and thus an additional 15 minutes on top of what was reported in Canadian preschoolers in a family care setting [33] would be close to 30 min/day, and ii) based on the evidence supporting that an additional 60 minutes per week of PA has been associated with improved aerobic fitness [19] and motor skills [19, 22, 44].

### Statistical analysis

The primary outcome measures will be differences between groups in overall PA and time spent in MVPA, a level of activity associated with health benefits. Secondary outcomes include differences in children’s time spent in sedentary behaviour (objectively measured by Actical accelerometer), height, weight, and body composition (body mass index, lean body mass, fat mass, and percent body fat). In addition, examination to determine if there are group differences in fundamental and gross motor skills will be conducted. Finally, daycare providers’ and parents’ attitudes, control beliefs, perceived competence (ability), and intentions toward incorporating PA into the daycare curriculum or home environments, will be assessed before and after the training workshops/webinars, as well as at 6-months post-workshop intervention.

#### Descriptive analysis

Baseline characteristics of the children and the daycare centres will be summarized descriptively. Categorical variables will be summarized using frequencies and percentages. Continuous variables will be summarized using means, standard deviations, medians, interquartile ranges, and ranges.

#### Primary analysis

To account for the cluster randomized design, a linear mixed effects model with a random effect for daycare will be used to compare time spent per day in MVPA at the 6-month follow-up between the daycare group and the control group. Potentially important child-level covariates will be included, namely age, sex, and participation in organized extra-curricular physical activities (dance, swimming, sport). Here, and throughout, a two-sided *P* value less than 0.05 will be deemed to be statistically significant. Analysis will follow the intention-to-treat principle, that is each daycare—and the children within that daycare—will be included in the group to which they were randomly assigned regardless of the adherence to the intervention.

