#### Comparison

Participating daycare centres that are randomized to the wait list control will continue to provide their regular curriculum during the study period. All comparison centres will be offered the ABC trial staff training and resources after the completion of data collection.

The primary outcome (MVPA) will be measured at baseline and at 3-months and 6 months post-intervention. The trial assessments and timeline are illustrated in Table 1. The baseline measurement will occur 2 weeks before the workshops to providers and parental webinars. This will include an assessment of PA and sedentary behaviour, body composition, fundamental and gross motor movement skills, and an assessment of the physical environment in daycare centres and homes as perceived by providers and parents, as well as attitudes, control beliefs, quality of life, perceived competency and intentions of providers and parents toward incorporating PA into the daycare curriculum and home environment, respectively. Immediately following the workshop and webinar training, attitudes, control beliefs, perceived competence, and intentions toward incorporating PA into the daycare setting and home environment will be measured. The parents receiving webinar training will be given an on-line ‘test’ to make sure they understood the training material. The components of the theory of planned behaviour, plus an assessment of any physical changes to the daycare or home environment (perceived by the provider or parent) will also be assessed at 6 months to determine the extent to which they predict PA at different time points. The 3-month evaluations will include children’s PA and sedentary behaviour, body composition and movement skills, as well as an evaluation of quality of life. The 6-month evaluation will include all of the 3-month measures and questionnaires, in addition to evaluations of the physical environment and theory of planned behaviour variables to examine associations with children’s PA.

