#### Secondary analyses

To account for PA at baseline, an analysis of covariance modelling approach will also be used (again including a random effect to account for clustering). These analyses will be repeated for the other outcome measures: time spent in sedentary behaviour, motor skills (measured by the TGMD-2)*,* anthropometrics (height, weight, body mass index, lean body mass, fat mass, percent body fat), physical environment (EPAO), and questionnaire data (attitudes, control beliefs, perceived competence, and intentions to increase PA). These analyses will be repeated for the same outcomes at the follow-up times. Predictive models for change in PA based on the questionnaire measures will also be developed. For all models, parameter estimates and 95% confidence intervals will be reported.

Specific to the cost analysis, the data of cost would include all the relevant costs of designing, implementing, monitoring, and analysing the RCT (labour/management cost, research cost, and capital cost). The cost effectiveness of the ABC intervention will be estimated using methods consistent with the guidelines established by the Panel on Cost-Effectiveness in Health and Medicine [80]. We will project costs as well as gains in both life-years and Quality-Adjusted Life Years (QALY) associated with the ABC intervention and with the no-intervention scenario. Health-related utility will be measured using the validated EuroQol five dimensions questionnaire (EQ-5D^TM^) index [81–83], which is a widely used questionnaire for calculating quality-adjusted life-years for assessing cost-effectiveness in healthcare.

Consistent with the panel’s recommendations, the societal perspective will be adopted, and future costs and benefits will be discounted to the present at an annual rate of 3%. The average relative performance of the ABC intervention will be assessed compared to no intervention, using a ratio of the additional expected cost of the program divided by the additional expected QALYs gained relative to the no-intervention alternative.

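### The primary model leaves out baseline MVPA, which is measured in every arm and used only in a secondary ANCOVA; the baseline-adjusted model should be primary

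*Protocol article*

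**What the plan says.** Under Primary analysis, a linear mixed model with a random daycare effect is "used to compare time spent per day in MVPA at the 6-month follow-up between the daycare group and the control group". The covariates are given as a closed list: "Potentially important child-level covariates will be included, namely age, sex, and participation in organized extra-curricular physical activities (dance, swimming, sport". Baseline MVPA does not appear.

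The baseline measurement exists. The Comparison section states: "The primary outcome (MVPA) will be measured at baseline and at 3-months and 6 months post-intervention". Table 1 ticks the activity monitor log at baseline, 3 months and 6 months in all three groups.

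Baseline adjustment appears only under Secondary analyses: "To account for PA at baseline, an analysis of covariance modelling approach will also be used", again with a random effect for clustering.

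On the participation covariate, the Questionnaires section says: "In addition to a simple baseline demographics questionnaire, we will ask all parents about their child’s involvement in extra-curricular activities". The same sentence goes on to "potential behaviour change at home (which will be validated by accelerometer data) so that we can account for participation in the analyses". No time point is given for either item, and Table 1 has no separate row for them.

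**The concern.** The two MVPA analyses differ mainly in whether baseline is used, and the article ranks the less efficient one first. With 12 centres in the primary contrast, randomization can easily leave the arms apart on baseline MVPA. The headline estimate would then carry part of that gap with no correction. If the primary and secondary estimates diverged for this reason, the trial would report two competing answers, with the weaker one holding confirmatory status.

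A smaller point concerns the participation covariate. Organized sport, dance and swimming can contribute to measured MVPA. A value recorded after the intervention starts could itself be affected by the intervention, and adjusting for it could distort the estimated effect. The text does not restrict the covariate to its baseline value.

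**Working it through.** **Inputs from the article (Sample size, Primary analysis):** 6 centres per arm, 15 children per centre on average, ICC 0.08, target difference 15 min/day, two-sided 5% error, 80% power.

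**Assumptions:** the SD, which is not given, and the correlation r between baseline and 6-month MVPA, which is also not given and is varied from 0.2 to 0.7.

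**1. The plan's own figure.** Design effect D = 1 + (15 − 1) × 0.08 = 2.12. Each arm has 6 × 15 = 90 children, an effective 90 / 2.12 = 42.45. Without an SD, the 12 centres cannot be reproduced independently. Solving for the SD that makes the claim true:

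SD = 15 / [(1.960 + 0.842) × √(2 / 42.45)] = 24.7 min/day (normal approximation).

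The same claim under a t distribution with 10 df (12 centres minus 2 arms) implies 22.2 min/day.

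**2. Standard error without baseline.** SE = 24.67 × √(2 / 42.45) = 5.35 min/day.

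**3. Chance baseline imbalance.** If baseline MVPA has the same SD and ICC, the between-arm baseline difference has the same SE, so its 95% range is ±1.96 × 5.35 = ±10.5 min/day, against a target effect of 15. The model without baseline carries about r times the realized gap. At r = 0.5, a gap at the edge of that range shifts the estimate by about 0.5 × 10.5 = 5.2 min/day.

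**4. Power with baseline in the model.** The variance is multiplied by 1 − r², with r equal at child and centre level. The last column starts from SD 22.2 and gives up one df for the baseline term.

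| r | 1 − r² | SE (min/day) | Power, normal, SD 24.7 | Power, t with 9 df, SD 22.2 |
|---|---|---|---|---|
| no baseline | 1 | 5.35 | 80% | 80% (10 df) |
| 0.2 | 0.96 | 5.25 | 81.6% | 80.6% |
| 0.3 | 0.91 | 5.11 | 83.6% | 82.6% |
| 0.5 | 0.75 | 4.64 | 89.9% | 89.0% |
| 0.7 | 0.51 | 3.82 | 97.5% | 97.1% |

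**5. Correlation at child level only.** The variance of a centre mean is proportional to 0.08 + 0.92 / 15 = 0.1413, and only the second term shrinks. At child-level r = 0.3 the ratio is (0.08 + 0.0613 × 0.91) / 0.1413 = 0.961. At r = 0.5 and 0.7 it is 0.892 and 0.787. Power (normal, SD 24.7) is then 81.5%, 84.3% and 88.4%.

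**The case against.** The strongest reply is that leaving out baseline is a choice of efficiency, not an error. Randomization makes the 6-month comparison unbiased either way, and the baseline-adjusted estimate is already planned with a confidence interval. This stands as far as bias goes. It does not explain why the less precise of two planned analyses holds primary status.

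Several stronger readings are tempting, and the article does not support them:

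- **That the primary analysis uses raw values.** It adjusts for age, sex and participation, and the Primary outcome variable section says the data are adjusted for wear time. Only baseline MVPA is missing.
- **That the 3-month data go unused.** They are outside the primary model, but Secondary analyses repeats the models at the follow-up times.
- **That the primary model adjusts for a mediator and is biased towards the null.** Collection of the participation covariate after randomization is possible but not shown. Table 1 has two baseline-only questionnaires, socio-demographic and pregnancy and lifestyle, that could hold the item. Behaviour change at home is not in the primary covariate list, and the home component is not part of the daycare-only versus comparison contrast. What remains is an open time point that is easily closed.
- **That omitting baseline leaves only 71% power.** That figure comes from putting the SD implied by a normal approximation into a t test with 10 df. It is a separate small-sample matter. Solved consistently, the starting point is 80% under either method.

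The cost also deserves a fair statement. ANCOVA needs a valid baseline recording (at least 5 hours on at least 3 days), so some children would be lost without a rule for missing baselines. Adding size, language and season as well would use about four centre-level parameters out of 12 centres, leaving roughly 6 df. That extension is not free and is not part of this point.

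**Conclusion.** The point holds as one of precision and protection against chance imbalance, not of bias. Moving baseline MVPA into the primary model would raise power from 80% to about 84%, 90% or 98% at r = 0.3, 0.5 or 0.7. The gain is smaller if the correlation is confined to children within centres, and close to nil if r is about 0.2 and a degree of freedom is given up. These figures rest on an SD inferred from the article's own power claim, an ICC of 0.08, 15 children per centre, and an assumed r. The direction of the gain is the same in every version tried; its size is not known. The timing of the participation covariate is a secondary matter of wording: the text permits a post-baseline value but does not establish one.

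**What to change.** Make the primary analysis a mixed model of 6-month MVPA on arm, baseline MVPA, age and sex, with a random daycare effect. Move the model without baseline MVPA to sensitivity. If extra-curricular participation stays as a covariate, state that its pre-randomization value is used.

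State how children without valid baseline accelerometry are kept, either by simple imputation of the baseline value or by a constrained-baseline model. This is the main cost. No new accelerometry is needed, and none for participation if that item is already asked at baseline.

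Trial status reports that the first cohort's 6-month data have been collected, so the change should be documented and dated before outcomes are compared by arm.

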### Assessment

#### Primary outcome variable

**Physical activity level** Physical activity levels of the preschoolers will be measured using omni-directional Actical^®^ accelerometers (mini Mitter Co., Inc., Bend, OR, USA). At each measurement period (baseline, 3- and 6-months post-workshop intervention), children will wear these activity monitors for a 7-day period. Study staff will train and assist the daycare providers and parents in correct placement of the accelerometer at the child’s time of arrival at the daycare centre on day 1. Data will be collected in 15-second epochs and Adolph et al.’s cut points [56] for preschool-aged children’s PA intensity will be applied to derive time spent at various intensities of movement (e.g., sedentary, light, moderate, vigorous) in harmony with the Canadian Health Measures Survey approach [57]. For ease of comprehension and comparison with other studies, activity data will be summarized and reported as activity minutes per hour, computed from tallied counts for each activity level mean across wear time. In line with current [57–59] and ongoing research in this population, [60] children with ≥5 hours of accelerometer data per day on at least 3 days will be included in the analyses and data will be adjusted for wear time.

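### The primary model uses only valid 6-month MVPA records, with no baseline term, although MVPA is also collected at baseline and 3 months

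*Protocol article*

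**What the plan says.** All places are in the Protocol article.

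- **Primary analysis.** A linear mixed model with a random effect for daycare will "compare time spent per day in MVPA at the 6-month follow-up between the daycare group and the control group". The covariates are age, sex and organised extra-curricular activity. The section adds: "Analysis will follow the intention-to-treat principle", and explains this as keeping centres and their children in the assigned arm whatever their adherence.
- **Primary outcome variable.** Monitors are worn for 7 days at each measurement period. Children with at least 5 "hours of accelerometer data per day on at least 3 days will be included in the analyses".
- **Comparison.** MVPA is scheduled at baseline, 3 months and 6 months.
- **Secondary analyses.** An analysis of covariance that accounts for baseline activity, also with a random effect for clustering, is secondary. Analyses at the follow-up times are separate repeats.
- **Sample size.** As a conservative choice, "the assumption is that there is an average of 15 preschoolers from each daycare". With an ICC of 0.08, 6 centres per group are "required to achieve a power of 80% to detect a difference between groups in MVPA of 15 min/day". No SD and no allowance for loss are given.

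**The concern.** The trial measures its primary outcome three times in each child but builds the primary test on one of them. A child who leaves the centre, is absent or does not wear the monitor long enough at 6 months drops out of that test, even with valid earlier records. The child's earlier activity, which says something about the missing value, is not used.

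Two things are at stake. The first is precision: baseline MVPA is usually among the best predictors of later MVPA, and with 12 centres in the comparison the trial has little precision to spare. The second is robustness: the stated model can allow for loss related to age, sex and extra-curricular activity, but not for loss that depends on earlier activity in a way that differs between arms. Wear and departure occur after randomisation, and providers in trained and wait-listed centres may differ in how well they support them.

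**Working it through.** **1. Which records reach which analysis.** I read the wear rule as applying at each measurement period, since the monitor is worn afresh each time.

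| Child's valid records | Stated primary model | Secondary ANCOVA at 6 months | Joint model of all visits |
|---|---|---|---|
| Baseline, 3 and 6 months | 6-month value only | baseline and 6-month values | all three |
| 6 months, no baseline | 6-month value | not used | all valid values |
| Baseline and 3 months | not used | not used | both |
| Baseline only | not used | not used | used, but adds almost nothing to the contrast |

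The third row is the point. Neither the primary model nor the secondary ANCOVA at 6 months uses that child. A separate 3-month analysis would, but it returns no information to the 6-month contrast.

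**2. What each model needs for an unbiased contrast.** The stated model holds if loss depends only on arm and its covariates; it can also hold if loss depends on activity in the same way in both arms. The ANCOVA additionally allows loss to depend on baseline activity. A joint model fitted by likelihood also allows dependence on observed 3-month activity. Each step is a weaker assumption.

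**3. The plan's own sample-size figure.** Inputs from Sample size: difference 15 min/day, 6 centres per arm, m = 15, ICC 0.08, power 80%, type I error 5%. The test is two-sided, since Primary analysis says "a two-sided *P* value less than 0.05 will be deemed to be statistically significant". The 6 per group cannot be reproduced forward because no SD is stated, so I solved for the SD that gives it.

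- Design effect D = 1 + (15 − 1) × 0.08 = 2.12
- Effective n per arm E = 6 × 15 / 2.12 = 42.5
- SD = 15 / [(1.960 + 0.842) × √(2/42.45)] = 15 / (2.802 × 0.2171) = 24.7 min/day, a standardised difference of 15/24.7 = 0.61

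Using t with 10 degrees of freedom (12 centres − 2 arms), the implied SD is 22.2. Rounding up to whole children and centres, an SD of about 22.4 to 24.5 gives exactly 6 per arm.

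**4. Effect of loss if 15 means enrolled.** The loss rates are assumptions. The SD is held at 24.7. Power = Φ(15 / [SD × √(2/E)] − 1.960).

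| Loss | m | D | E = 6m/D | SE | Power |
|---|---|---|---|---|---|
| 0% | 15 | 2.12 | 42.5 | 5.35 | 80.0% |
| 20% | 12 | 1.88 | 38.3 | 5.64 | 75.8% |
| 30% | 10.5 | 1.76 | 35.8 | 5.83 | 73.0% |

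The t-based version, with its own back-solved SD, agrees within 0.1 percentage point. The drop is modest because the design effect falls as children are lost. Keeping 15 analysable would need 15/0.8 = 18.75, so 19 enrolled per centre at 20% loss, or 15/0.7 = 21.4, so 22 at 30%.

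**The case against.** **A reader might infer that the intention-to-treat claim is contradicted.** It is not. Primary analysis defines the term by assigned group and adherence, in contrast to the later per-protocol set. A rule for what counts as a valid measurement does not breach that definition. The label simply does not describe which children have an outcome.

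**A reader might infer that fewer than 15 per centre will be analysed.** The documents do not show this. The 15 is an assumed average, called conservative, drawn from centres said to enrol 10 to 40 preschoolers, and children must plan to stay at least 6 months. It may already be the analysed number.

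**A reader might infer a biased primary result.** That would need loss rates by arm and a difference between lost and retained children. The article gives neither, so I put no figure on bias.

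**A single-visit primary analysis is legitimate.** It is simple, and the secondary ANCOVA already uses baseline activity. This stands as a defence of validity. It does not explain why the less precise analysis, which leaves out relevant data already collected, should be primary.

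**Missing-data methods may sit in a full protocol or SAP not shown.** Agreed: the absence of a sensitivity analysis or an attrition figure is not held against the article. The point concerns the primary model that it does state.

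**A joint model has its own risk.** With 12 centres, random effects for centre and child alone can understate the standard error of the 6-month contrast, because centres also change differently over time. This stands, and the fix allows for it.

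**Conclusion.** The point holds as a question of method. The stated primary model is an available-case comparison at one visit. It leaves baseline MVPA to a secondary analysis and lets 3-month MVPA play no part in the 6-month contrast. A better primary model is available from data already collected, and adopting it is worthwhile rather than essential.

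The gain in precision cannot be quantified, because no within-child correlation is stated. The loss of about 4 power points at 20% and 7 at 30% is illustrative only. It assumes that 15 means enrolled, an ICC of 0.08, equal loss in every centre and a back-solved SD. If 15 is the analysed number, that part falls away and the point about the model remains.

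**What to change.** 1. Make the primary analysis a linear mixed model on all valid MVPA records at baseline, 3 and 6 months. Include arm by time, a common baseline mean, and the age, sex and extra-curricular covariates already named; keep the stated wear-time adjustment.
2. Include random effects for centre, centre-by-time and child. Use small-sample degrees of freedom (for example Kenward-Roger or Satterthwaite) suited to 12 centres.
3. Keep the 6-month DC versus COM contrast as the primary test.
4. Describe the analysed set as children with valid records, analysed as randomised.
5. State whether 15 per centre is before or after loss.

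**Cost.** No new data; revised wording and a larger model, with more variance components to estimate from few centres. Timing matters. By the dates in Trial status and the counts in Randomization, the two cohorts with 6-month follow-up dated by May 2014 hold 8 + 7 = 15 of the 18 centres. Of the 12 DC and COM centres they hold (3 + 2) + (2 + 3) = 10. The change must therefore be fixed and dated before any unblinded analysis, with the reason recorded.
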